## Abstract

**Background:**

The relationship between dietary components and nonalcoholic fatty liver disease (NAFLD) needs to be further investigated. The potential health benefits of cardamom have been found in some studies. Cardamom showed beneficial effect on hepatomegaly, dyslipidemia, and fasting hyperglycemia in animals. However, some adverse effects of cardamom have been reported in animals. No previous human study had been conducted on the effects of cardamom in NAFLD. This study aims to determine the effects of green cardamom (*Elettaria cardamomum*) supplementation on blood glucose indices, lipids, inflammatory profiles, and liver function, especially by examining irisin, paraxonase-1 (PON1) and sirtuin-1 (Sirt1) in obese patients with NAFLD.

**Methods:**

This trial is to be conducted at the polyclinic of the National Iranian Oil Company (NIOC) Central Hospital, Tehran. Eighty obese patients with NAFLD will be selected according to the eligibility criteria. The NAFLD diagnosis method is ultrasonography. Patients will be randomly divided into two groups by a random-number table (cardamom and placebo groups, two 500-mg capsules, three times/day, taken with meals for 3 months, follow-up monthly). General characteristics, dietary intakes (at the beginning, middle, and end), and physical activity (at the beginning and end) will be assessed using a general, 24-h food recall, and short-form International Physical Activity Questionnaires (IPAQ), respectively. Lifestyle advice will be presented to both groups identically. At the beginning and the end, anthropometrics (weight, height, and waist circumference), blood pressure, extent of fatty liver, and blood biomarkers, including serum glucose indices (fasting blood sugar (FBS)) and insulin (FBI), homeostasis model assessment-insulin resistance (HOMA-IR), Quantitative Insulin Sensitivity Check Index (QUICKI)), lipids (triglyceride (TG), low-density lipoprotein-cholesterol (LDL-c), high-density lipoprotein-cholesterol (HDL-c), total cholesterol (TC)), inflammatory markers (highly sensitive C-reactive protein (hs-CRP), tumor necrosis factor-alpha (TNF-α), interleukin-6 (IL-6)), liver enzymes (alanine transaminase (ALT), aspartate transaminase (AST)), irisin, PON1, and Sirt1, will be determined.

**Discussion:**

This trial would be the first to assess the effects of green cardamom on several blood factors, including glucose indices, lipids, inflammatory markers, liver enzymes, irisin, PON1, and Sirt1, and blood pressure and anthropometry in obese patients with NAFLD. Further study of cardamom’s potential in improving NAFLD is suggested.

**Trial registration:**

Iranian Registry of Clinical Trials (IRCT), ID number: IRCT2015121317254N4. Registered on 27 December 2015.

**Electronic supplementary material:**

The online version of this article (doi:10.1186/s13063-017-1979-3) contains supplementary material, which is available to authorized users.

## Background

NAFLD is engendered due to the accumulation of large amounts of triglycerides in liver cells (5% <) [1]. The prevalence of NAFLD is currently increasing [2] (an average of 30% in Iranian adults [3, 4]). NAFLD prevalence in obese (Body Mass Index (BMI) ≥25) and nonobese (BMI <25) adults has been reported as being approximately 65–85% and 15–20%, respectively [5]. The pathology of NAFLD is a two-stage phenomenon, including the accumulation of fat in hepatocytes and subsequent hepatic steatosis in the first stage, and nonalcoholic steatohepatitis (NASH) in the second stage. Insulin resistance plays a key role in both stages and oxidative stress and proinflammatory cytokines are major stimulating components of the pathology [6]. NAFLD, being a major health problem, includes a wide range of clinical symptoms (from the asymptomatic fatty liver to severe inflammation along with fibrosis and sometimes cirrhosis). Often, these patients are insulin-resistant [7]. Insulin resistance is directly correlated with the content of fat in the liver. Nuclear factor kappa-light-chain-enhancer of activated B-cells (NF-κB) is a protein complex responsible for cytokine production and cell survival. Known triggers of NF-κB include reactive oxygen species (ROS), tumor necrosis factor-alpha (TNF-α), interleukin-1 beta (IL-1β), bacterial lipopolysaccharide, isoproterenol, cocaine, and ionizing radiation. NF-κB activation upregulates the production of proinflammatory cytokines that affect both local and systemic insulin action. This means that inflammation, adipokines, oxidative stress, and lipid metabolites can affect insulin sensitivity, but are not necessarily directly associated with intrahepatic fat content [5]. Most patients with NAFLD have metabolic syndrome characteristics, including being overweight and obese, impaired glucose tolerance, hyperlipidemia and hypertension [8, 9]. Other risk factors of NAFLD are age, family history, malnutrition, severe weight loss, the consumption of certain medicines, certain diseases [10], and gastrointestinal microbiota [11].

Along with increasing oxidative stress, both the activity and production of bonded-to-high-density lipoprotein-cholesterol (HDL-c) blood PON1 is suppressed in patients with NAFLD [12, 13]. PON1 has an anti-inflammatory role by interfering with the production of inflammatory factors [12]. PON1 is activated by peroxisome proliferator-activated receptor gamma (PPAR-γ) [14] and, according to previous studies, the intake of dietary polyphenols (particularly flavons) is associated with increasing PPAR-γ [15–17].

Irisin is a newly identified myokine related to exercise. Recently, it was reported that serum irisin levels have shown associations with intrahepatic triglyceride content which is indicative of it playing an important hepatic role [18]. According to recent studies, irisin plays a role in insulin sensitivity [18–22] through effects on glucose and lipid metabolism [19, 23] and increased thermogenesis [19, 20, 24]. Its secretion can be increased by lifestyle modifications, regular exercise [20–22, 24, 25], and stress [21]. In a human study, serum irisin levels were inversely associated with the triglyceride (TG) content in the liver and liver enzymes in obese adults (aged 40 years and older) with NAFLD [26].

Sirtuins have seven categories, of which Sirt1 has mainly been identified and studied in humans [27]. Sirt1, as a histone deacetylase class III, decreases oxidative stress indirectly through catalase and superoxide dismutase (SOD) [28]. Sirt1 activation has beneficial health consequences such as improved insulin sensitivity, obesity reduction, increased mitochondrial function, decreased glucose levels, and increased physiological functions [29, 30]. Sirt1 plays an important role by increasing PPAR-γ co-activator-1 alpha (PGC-1α) [27, 29]. Usually, polyphenols activate Sirt1 and, subsequently, PGC-1α also inhibits NF-κB [29, 31].

Dietary polyphenols including derivatives and isomers of flavones, isoflavones, flavonoids and catechins and phenolic acids have antioxidant and anti-inflammatory properties [32]. Green cardamom (*Elettaria cardamomum*) contains phenolic and flavonoid compounds, such as flavonols (quercetin and kaempferol), flavone (luteolin) and anthocyanidin (pelargonidin) [33], that are inhibitors of NF-κB [33–36]. Isoflavones and flavonoids, such as quercetin, resveratrol [37], and kaempferol, increase the activity of PGC-1α [38]. On the other hand, irisin secretion increases in response to increasing PGC-1α [25]. Owing to the effect of dietary polyphenols on PGC-1α, it is possible that green cardamom polyphenols will be able to influence thermogenesis and improve insulin resistance. Moreover, in cell studies, irisin effectively prevents hepatic steatosis by lipogenic gene expression changes and oxidative stress inhibition [18]. In addition, irisin leads to fibroblast growth factor-21 (FGF-21) upregulation through the PPAR signaling pathway, especially PPAR-α [22], which can subsequently improve insulin sensitivity and hepatic steatosis [22, 26].

Lifestyle changes—including gradual weight loss and increasing physical activity—are common ways to reduce and treat NAFLD [39–43]. Since achieving weight loss and maintaining a reduced weight for a long time is difficult [44], it seems that dietary changes may be a proposed therapeutic approach for these patients [45]. Some studies were conducted on green cardamom’s role in health as a spice. The effects of cardamom reported by those studies are blood pressure lowering, fibrinolysis enhancing, antispasmodic effects, and gastroprotective, antibacterial, antioxidant [46], anti-inflammatory, anti-food poisoning, carminative, diuretic, expectorant, heart-function improving, anticarcinogenic [47], and antiplatelet aggregation effects [48]. Cardamom volatile oil contains terpenes, esters, flavonoids and other compounds. The major constituents of the volatile oil of cardamom include about 36% 1,8-cineole, 31% alpha-terpinil acetate, 12% limonene, 3% sabinene and others. Most studies have been conducted on the 1,8-cineole compound. The reported effects are apoptotic, the inhibiting of cytokines, prostaglandins, leukotrienes, and nitric oxide (inhibition of cyclooxygenase-2 (COX-2) and inducible nitric oxide synthase (iNOS)), TNF-α and IL-1β inhibition, liver necrosis reduction, cardiovascular effects (blood vessel relaxation), as well as anticholinergic effects and the blocking of muscarinic receptors [49].

The hypothesis is that the antioxidant, anti-inflammatory, antibacterial, and hypolipidemic activities of cardamom can improve NAFLD. The effects of cardamom on Sirt1 secretion and, subsequently, PGC-1α, irisin, and insulin sensitivity are not clear. Moreover, its effects on PPAR-γ and, subsequently, serum PON1 levels need further study. With an awareness that NAFLD increases in overweight or obese populations, and the lack of human studies on the effects of green cardamom, this clinical trial study was planned to determine its impact on blood glucose indices, lipids and inflammatory profiles, liver function, and insulin resistance, especially through irisin, PON1, and Sirt1.

## Methods

### Study design and objectives

A double-blind randomized clinical trial design is to be used in this study.

### Objectives

× Compare the mean serum lipid (triglycerides (TG), total cholesterol (TC), low-density lipoprotein (LDL), high-density lipoprotein (HDL)) and glucose indices (fasting blood sugar (FBS), fasting blood insulin (FBI), homeostasis model assessment-insulin resistance (HOMA-IR), Quantitative Insulin Sensitivity Check Index (QUICKI)) between the two groups and within each group, before and after intervention× Compare the mean serum inflammatory factors (TNF-α, interleukin-6 (IL-6), highly sensitive C-reactive protein (hs-CRP)) between the two groups and within each group, before and after intervention× Compare the mean of serum PON1, sirt1, and irisin between the two groups and within each group, before and after intervention

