### The sample size

The sample size was calculated using the “two mean comparison formula” and was related to a previous study [52] which had assessed the effects of cardamom on lipid profiles. In this study, the errors I and II are considered to be 0.05 and 0.2, respectively. The mean difference of TG between the groups was 5 mg/dl, and the standard deviation of each group was 8 mg/dl. The sample size was determined to be 40 subjects in each group. In total, 80 patients were invited and randomly divided into two groups as follows:Forty overweight or obese patients with NAFLD will be given lifestyle change recommendations (weight-loss diet (5%) during the study and increasing physical activity) and a green cardamom supplement for 3 monthsForty overweight or obese patients with NAFLD will be given lifestyle change recommendations (weight loss diet (5%) during the study and increasing physical activity) and a placebo supplement for 3 months

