### Data analysis

Data entry, coding, security, and storage are also to be considered. The normality of continuous variables will be determined using a Kolmogorov-Smirnov test. Continuous and categorical baseline characteristics of the groups will be assessed using a *t* test and a chi-square test, respectively. Multivariate, two-factor, repeated measures analysis of variance will be used to assess time effects and to analyze time × treatment interaction effects on all dependent variables. All statistical measurements will be reported with 95% confidence interval (CI). A *P* value < 0.05 will be considered as statistically significant. The data will be analyzed by using SPSS software.

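### Within-group before/after comparisons and time effects stand unranked beside the randomised contrast, although both arms receive the same weight-loss and exercise programme

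*Protocol article*

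**What the plan says.** The Objectives section sets three objectives covering 14 serum markers: eight lipid and glucose indices, three inflammatory factors, and PON1, Sirt1 and irisin. All three end in the same way. The third reads "Compare the mean of serum PON1, sirt1, and irisin between the two groups and within each group, before and after intervention", and the second closes with "highly sensitive C-reactive protein (hs-CRP)) between the two groups and within each group, before and after intervention". Nothing says which comparison decides.

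The Data analysis section plans a two-factor repeated measures analysis of variance that "will be used to assess time effects and to analyze time × treatment interaction effects on all dependent variables". One threshold covers everything: "A *P* value < 0.05 will be considered as statistically significant". No sentence confines within-group or time results to description.

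Both arms receive the same background programme. The abstract says "Lifestyle advice will be presented to both groups identically". The sample size section gives the placebo arm the "weight loss diet (5%) during the study and increasing physical activity) and a placebo supplement for 3 months", and gives the cardamom arm the same diet and activity advice with cardamom in place of placebo. The Background describes gradual weight loss and more physical activity as common treatments for NAFLD and says of irisin, one of the objective markers, "Its secretion can be increased by lifestyle modifications, regular exercise". The exclusion criteria remove people who already exercise regularly, so the exercise advice is new to participants in both arms.

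**The concern.** A before/after change in the cardamom arm is the sum of any cardamom effect and whatever the diet and exercise programme does. By the protocol's own account the second part is unlikely to be zero, least of all for irisin. The time main effect averages the change over both arms, so it measures mainly the shared programme. Neither quantity separates cardamom from lifestyle advice.

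As written, a positive result on either would still answer a stated objective at the trial's own significance threshold. At stake is a report that cardamom improved a marker because the marker moved significantly in that arm, or moved significantly there and not under placebo, when the randomised comparison shows nothing. With 14 markers and two arms there are 28 such within-arm comparisons beside 14 between-arm ones.

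**Working it through.** **The plan's own figure.** Inputs from the sample size section: difference in TG 5 mg/dl, SD 8 mg/dl, type I error 0.05 (two-sided assumed), type II error 0.2. Then n per arm = 2 × 8² × (1.960 + 0.842)² / 5² = 40.19, which is 41 rounded up, against 40 stated. Power at 40 per arm is 79.8% by the normal formula and 78.8% by the exact t calculation. The figure reproduces closely, and it was derived for a between-group difference.

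**Set-up.** No cardamom effect; 40 per arm; both arms share a mean change of d, in units of the SD of change. The protocol gives no size for d, so it is varied from 0.1 to 0.8.

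- Within-arm paired t test: 39 df, critical value 2.023, noncentrality d × √40. Let p be the probability of P < 0.05.
- Significant in cardamom and not in placebo: p × (1 − p), as the arms are independent.
- Pooled time effect: 78 df, critical value 1.991, noncentrality d × √80.
- Between-arm difference in change, which with two time points is the time × treatment interaction: the shared change cancels, so the rate is 5% two-sided, or 2.5% in favour of cardamom, for every d.

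| d | p, cardamom arm | cardamom only | pooled time effect |
|---|---|---|---|
| 0.1 | 9.5% | 8.6% | 14.3% |
| 0.2 | 23.5% | 18.0% | 42.4% |
| 0.3 | 45.7% | 24.8% | 75.5% |
| 0.4 | 69.4% | 21.2% | 94.2% |
| 0.5 | 86.9% | 11.4% | 99.3% |
| 0.6 | 95.9% | 3.9% | >99% |
| 0.7 | 99.1% | 0.9% | >99% |
| 0.8 | 99.9% | 0.2% | >99% |

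Worked line, d = 0.3: the noncentrality is 0.3 × √40 = 1.90, so p = 0.457 and 0.457 × 0.543 = 0.248.

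**On the TG scale.** Take the protocol's SD of 8 mg/dl and assume a before/after correlation r. The SD of change is 8 × √(2(1 − r)): 9.47, 8.00 and 6.20 mg/dl for r = 0.3, 0.5 and 0.7. A shared fall of 2 mg/dl makes the cardamom arm significant in 26%, 34% and 51% of trials. A shared fall of 5 mg/dl, the size of the planning difference, does so in 90%, 97% and over 99%.

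**Simulation check.** With 40,000 trials, a shared change of 2.5 mg/dl and r = 0.5, the cardamom arm was significant in 49.1%, cardamom only in 24.8%, and the between-arm test in 4.99%. The corresponding formula values are 48.7%, 25.0% and 5%.

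**The case against.** The strongest reply is that the valid analysis is already in the plan. The same sentence that mentions time effects goes on to the time × treatment interaction for every dependent variable, and with baseline and end values that interaction is the between-arm difference in change. Each objective names the between-group comparison first, the sample size rests on a between-group difference, and placebo, blinding and identical advice all serve that contrast. This stands: the randomised comparison is neither absent nor wrongly specified.

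A reader might infer that the investigators intend to treat a within-arm change or a time effect as proof of efficacy. The protocol does not say so. It makes these comparisons objectives and leaves their role open.

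Nor does the analysis section name a paired test for each arm. The model's time effect is pooled, so on its own it cannot produce a result that is significant under cardamom and not under placebo. The paired-test figures therefore rest on reading the within-group objective as a test, which is plausible but not fixed.

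The cardamom-only pattern is also not uniformly common. It peaks at 25% and falls below 1% from 0.7 SD upward, because both arms then become significant. A strong lifestyle effect makes that particular misreading rare, while making the within-cardamom result on its own almost certain.

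Finally, one might add regression to the mean as a cause of within-arm change. Eligibility sets no threshold on any of the 14 markers, so the protocol does not show that it matters here, and the point does not need it.

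**Conclusion.** The point holds as a fault in how the objectives and tests are framed. Comparisons that cannot isolate cardamom stand as unranked objectives at the same threshold as the one that can. This is more than missing detail, because the within-group comparison is written into all three objectives and the time effect into the analysis.

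Over an assumed shared shift of 0.1 to 0.8 SD of change, a trial of an inert supplement would give a significant within-cardamom change in about 10% to over 99% of cases for each outcome. It would give the cardamom-only pattern in about 0.2% to 25%. The between-arm test holds 5% throughout. These rates assume 40 analysed per arm, normally distributed changes, a two-sided 0.05 test and an equal shift in both arms. The size of the shift is an assumption. That within-arm tests have an inflated error rate for cardamom holds for any non-zero shared shift.

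Since the planned interaction answers the randomised question, the point is a correction that should be made, not a defect that invalidates the trial.

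**What to change.** 1. In the Objectives, restrict each of the three comparisons to the two groups and remove the within-group testing.
2. In the Data analysis section, state that every conclusion about cardamom rests only on the between-arm contrast: either the month-3 value adjusted for baseline or the time × treatment interaction already planned. Either choice is valid and both use values already collected; name one.
3. State that within-arm mean changes and time effects are reported descriptively, without P values, and are not evidence for or against cardamom.

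The trial is registered and was recruiting when the article was submitted, so this is a dated wording amendment to the protocol, with the registry entry updated if it carries the same objectives. It needs no new data, reduces the number of tests and leaves the sample size unchanged, since that was already set on a between-group difference.

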### Inclusion criteria

× NAFLD diagnosed by a radiologist and a hepatologist using ultrasonography, and divided into one of three categories (mild, moderate or severe degree)× Age 30–60 years× Overweight or obese (25 ≤ BMI < 35)× Informed consent signed and dated by the subject and investigator

### Exclusion criteria

× History of alcohol consumption during the preceding 12 months, based on patient’s own evidence× Suffering from cognitive impairment or other psychotic illnesses, as diagnosed by a psychiatrist× Severe depression, lacking the ability to cooperate and answer questions× Diagnosed pathological conditions affecting the liver such as viral hepatitis, acute or chronic liver failure, cholestasis, liver transplantation, habitual abuse of nonsteroidal anti-inflammatory drugs, antibiotics, antisecretory drugs causing achlorhydria within 3 months before the study, corticosteroids, amiodarone, valproate, prednisone, tamoxifen, perhexiline and methotrexate, rapid weight loss, diabetes, heart failure, thyroid disorders, kidney disease, respiratory failure, psychological disorders, hereditary hemochromatosis and Wilson’s disease, alpha-1 antitrypsin deficiency, autoimmune diseases, celiac disease, use of liver fat inducers, and hormonal drugs× Acute systemic disease, cystic fibrosis, muscular dystrophy, protein malnutrition, a history of gastrointestinal surgery, neurological disorders, structural abnormalities of the gastrointestinal tract× NAFLD caused by secondary factors including drugs, surgical procedures, environmental toxins, and total parenteral nutrition (TPN)× Conditions leading to physical inactivity (disability)× Uncontrolled hypertension (>140/90 mmHg)× Any diagnosed malignancy× Breast feeding, pregnant, and/or planning for pregnancy in the following 3 months× Professional athlete or doing regular exercise× Treatment with statins, antihypertensive drugs, ursodeoxycholic acid, probiotics, and multivitamin-mineral and antioxidant supplements during the past 3 months× Surgery for weight loss in the past year and weight loss in the past 3 months× Intake of drugs that interact with cardamom including aspirin, anticoagulants (warfarin, heparin) and antiplatelet (clopidogrel), nonsteroidal anti-inflammatory (ibuprofen or naproxen), blood pressure-lowering drugs, central nervous system (CNS) depressants (benzodiazepines such as lorazepam or diazepam, barbiturates such as phenobarbitals, narcotics such as codeine, some antidepressants and alcohol), anaesthetics, antibiotics, anticancer agents, anticholinergics, antifungals, cyproheptadine, diuretics (loop), estrogen, indomethacin, muscarinic agents, pain relievers and prednisolone× Taking a multivitamin-mineral or antioxidant supplement at least once a week during the study× Not taking more than 10% of prescription supplements

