## Randomization and intervention

Patients are divided into two equal groups using block randomization. Stratified randomization will be used to control age and gender distribution. In this study, the ratio of green cardamom and placebo supplementation groups is 1:1. The block randomization is performed by an assistant and the intervention allocation is blinded for both the investigator and subjects. The participants are randomly placed into two groups receiving whole green cardamom powder or toast powder supplements. Cardamom and placebo capsules are prepared by the Traditional Medicine Research Center (TMRC), Iran University of Medical Sciences. Each capsule contains 0.5 g of whole green cardamom or toast powder. Placebo and cardamom capsules are similar in shape, size, and color. At the beginning of the study, all placebo capsules are to be placed near the cardamom capsules so that the patients are able to smell them. Even though some cardamom volatile oils may be absorbed by the placebo capsules, this amount is considered negligible compared to the amounts that affect health indicators. The type of supplements is blinded as A and B packages for investigators and patients.

According to previous trials, the dose of whole green cardamom powder was determined to be 3 g per day [46, 52, 53]; two capsules were consumed with each meal.

The voucher number of green cardamom is *Elettaria cardamomum* (L.) Maton, Family: Zingiberaceae, PMP-669. An essential oil percentage and the total content of phenolic and flavonoid compounds of green cardamom will be assessed using high-performance liquid chromatography (HPLC) and gas chromatography mass spectrometry (GC-MS) in the institute of medicinal plants, Shahid Beheshti University of Medical Sciences, Tehran, Iran. Some polyphenolic compounds of green cardamom, whose effects have been mentioned in other articles (caffeic acid, gallic acid, quercetin and luteolin), will also be determined by using HPLC.

Supplements are to be distributed among patients once a month and their potential complications and consumption processes registered (number of consumed capsules and the returned packages). In addition, the consumption process is to be checked once a week, by telephone.

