## Discussion

This trial will first assess the effects of green cardamom (*Elettaria cardamomum*) on blood glucose indices, lipids, inflammatory factors, paraxonase-1, sirtuin-1 and irisin in overweight or obese patients with nonalcoholic fatty liver disease (NAFLD). The different clinical usages and the lack of awareness concerning the advantages and disadvantages of green cardamom in patients with NAFLD makes this study very pertinent. Although there is a hypothetical reason for using green cardamom in the treatment of some disorders, its therapeutic use in humans necessitates the study of its potential in different diseases, particularly NAFLD. Attention should be paid to the increasing rates of obesity (and, consequently, NAFLD). Due to remarkable changes of some blood markers in this population, and the lack of human studies on the effects of green cardamom, this trial selected these patients as the most suitable cases for intervention.

The strengths of the study are its randomized double-blinded design, protocol publication, the measurement of dietary outcomes and physical activity status, and the recording of patient-reported probable complications.

The limitations of the study are self-reporting of diet and physical activity, slow patient recruitment because of the eligibility criteria, a single center and lack of cooperation by some patients at the end, which may lead to these patients needing to be being replaced.

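### Two exclusion criteria can only be met after randomisation, and the article foresees replacing patients, so applying the text as written puts the randomised comparison at risk of selection bias

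*Protocol article*

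**What the plan says.** The Exclusion criteria section of the protocol article mixes baseline conditions with two that arise later: "Taking a multivitamin-mineral or antioxidant supplement at least once a week during the study" and "Not taking more than 10% of prescription supplements". The same list already has a proper baseline item on supplements, covering "multivitamin-mineral and antioxidant supplements during the past 3 months", so the on-study item is a separate rule and not a restatement.

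Randomization and intervention shows when adherence becomes known. Capsules are handed out monthly, with patients' "their potential complications and consumption processes registered (number of consumed capsules and the returned packages", and intake is checked weekly by telephone.

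The limitations paragraph of the Discussion mentions "lack of cooperation by some patients at the end, which may lead to these patients needing to be being replaced". No way of allocating replacements is described.

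The sample size section states "The sample size was determined to be 40 subjects in each group" and gives no allowance for loss. Study blood is drawn only at the start and at the end of the three months.

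**The concern.** An exclusion criterion that is met only after allocation works as a removal rule. Patients who stop taking capsules or start other supplements may differ in outcome from those who do not. All patients also receive a weight-loss diet and activity advice, so capsule adherence may track diet adherence, and the outcomes include lipids and glucose indices. If the kind or number of patients removed differs by arm, the remaining groups are no longer those that randomisation formed.

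This acts during conduct, not only at analysis. A patient dropped before the final visit has no month-3 sample, and no later analysis plan can supply one. Replacing such a patient restores the count of 40 but not the randomised comparison.

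The adherence item is also unclear in itself. It may mean patients who took 10% or less of their capsules, or patients who missed more than 10%. Two staff members could apply it very differently.

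**Working it through.** **Inputs from the article.** Two-sided alpha 0.05 (sidedness is not stated; two-sided is assumed), type II error 0.2, TG difference 5 mg/dl, SD 8 mg/dl, 40 per group, two capsules three times a day for 3 months. The planned effect is 5/8 = 0.625 SD.

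**The plan's own figure.** n = 2 × [8 × (1.960 + 0.842)/5]² = 40.19 per group, or 41 rounded up. The stated 40 gives 79.8% power by normal approximation, so the sample size is not in dispute here.

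**The two readings of the adherence item.** Taking 3 months as 90 days, 6 × 90 = 540 capsules.
- Took 10% or less: cut-off 0.10 × 540 = 54 capsules.
- Missed more than 10%: cut-off 0.90 × 540 = 486 capsules, so a patient is removed after missing more than 54/6 = 9 days' worth.

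Both readings are settled only after randomisation, so the main point does not depend on which was meant.

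**Bias under no true effect.** Let f be the share removed and d the mean of removed minus retained patients in an arm. The retained mean is then off by −f × d. With the same f in both arms, the between-arm bias has size f × D, where D is the difference in d between arms. Type I error is Φ(−1.96 + b/se) + Φ(−1.96 − b/se), with b in SD units, se = √(2/n) and n = 40(1 − f). The article gives neither f nor D, so every value below is an assumption.

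| f | D (SD) | Bias (SD) | Bias (mg/dl) | Share of 0.625 SD | n per arm | Type I error |
|---|---|---|---|---|---|---|
| 0.10 to 0.20 | 0 | 0 | 0 | 0% | 36 to 32 | 5.0% |
| 0.10 | 0.5 | 0.05 | 0.4 | 8% | 36 | 5.5% |
| 0.15 | 1 | 0.15 | 1.2 | 24% | 34 | 9.5% |
| 0.20 | 1 | 0.20 | 1.6 | 32% | 32 | 12.6% |

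**A second route: same d in both arms, unequal removal.** Bias = (fA − fB) × d, with d = 8 mg/dl (1 SD).
- 20% against 10% removed: 0.10 × 8 = 0.8 mg/dl, type I error about 7.0%.
- 30% against 10% removed: 0.20 × 8 = 1.6 mg/dl, type I error about 12.5%.
- Equal removal: bias zero.

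If arms are refilled to 40 with patients like those retained, a bias of 1.6 mg/dl stays and type I error is about 14.5%, because the standard error shrinks.

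**Power if nobody is replaced.** Power = Φ(0.625 × √(n/2) − 1.96).
- 10% loss, n = 36: Φ(2.652 − 1.960) = 75.5%.
- 20% loss, n = 32: Φ(2.500 − 1.960) = 70.5%.

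**The case against.** The article nowhere says that these patients are dropped from the analysis. The two items might be meant only as rules for ending participation, and analysis sets are commonly left to an analysis plan or full protocol that is not shown. That is fair: the lack of a defined analysis set is no fault here. What stands is that the text lists post-randomisation events as grounds for exclusion, and following it can cost the final blood sample.

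A reader might infer that the analysed groups will certainly be selected, that replacement is an operating rule which breaks the stratified blocks, and that it conceals losses behind a constant 40. The documents do not support this. The replacement remark is conditional, stands in a limitations paragraph and discloses the problem openly. A newcomer could be given the next code in the stratum, and nothing says that losses will go unreported.

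The design also lowers the risk of differential removal. Patients and investigators are blinded, packages are coded A and B, capsules look alike, and placebo is stored near the cardamom to mask the smell. The most plausible link with outcome, that capsule adherers also follow the diet, acts in both arms and pushes D towards zero. A D of 1 SD needs, for example, removed patients 0.5 SD above retained ones in one arm and 0.5 SD below in the other. These points make zero bias a credible case; they do not make it certain.

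**Conclusion.** The point holds as a conditional risk. Two exclusion criteria rest on behaviour after randomisation, one of them has two incompatible readings, and replacement is foreseen without a rule. If they are applied as written, the between-group comparison is exposed to selection bias.

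The plausible range runs from no bias and 5.0% type I error to about 0.2 SD (32% of the planned effect) and about 12-13%. The upper end assumes 20% removal with a 1 SD between-arm difference, or 30% against 10% removal with removed patients 1 SD away in both arms. Refilling would take it to about 14.5%. It might be inferred that the trial's true error rate is inflated. The documents cannot show that, since they give no removal rate and no outcome difference. Confidence is high on the wording defect and low on the amount of bias.

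**What to change.** - Limit the exclusion criteria to facts known before randomisation. Record on-study supplement use and non-adherence as protocol deviations.
- Seek the month-3 blood draw from every randomised patient, whatever their adherence or supplement use, and analyse all as allocated. For missing month-3 values, use a likelihood-based mixed model or multiple imputation that includes baseline, arm, age and sex.
- Reconcile the adherence wording to one definition and use it only for a per-protocol sensitivity analysis.
- Do not substitute new patients for randomised ones in the primary comparison. Recruitment was under way at submission, so report by arm, with reasons, anyone already removed or replaced.

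**Cost.** Wording and analysis only, with no new visits. The estimate will include non-adherers. Without a loss allowance, the stated 80% power should be restated as about 75.5% at 10% loss or 70.5% at 20% (assumed rates). The alternative is to set a larger randomised total in advance: 40/0.90 = 44.4, so 45 per group at 10% loss, or 40/0.80 = 50 at 20%. That costs 10 or 20 more patients, in a trial that already names slow recruitment as a limitation.
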